### **3.10 Data analysis**

The collected data and will be analyzed using IBM Statistical Package for Social Science (SPSS) version 25 involving descriptive and inferential statistics. Descriptive statistics will be used to describe the characteristics of participants. Whilst, the descriptive analysis for continuous variables with mean, mode, median and percentage will be analyzed.

The bivariate analysis of Chi-square will be used to measure associations between two categorical variables. A generalized Linear Mixed Model (GLMM) then will be conducted to determine the effects of sociodemographic factors (age, gender, ethnicity, level of education), socioeconomic (employment status, household income), working experience (duration) and previous training (training attended) on KAP on occupational safety and health at food premises among food handlers pre and post intervention within and between study groups.

In further analysis, the effects of SCT constructs component as the base of the theory-based intervention module which is behavior, individual and environment factors on KAP on occupational safety and health at food premises among food handlers pre and post intervention within and between study groups will be determined.

The effects that are going to be determined is fixed and random effects. The fixed effect is factors that the only level under consideration are continued in coding those effects. For example, both male and female genders are included in the factor sex; other examples as different ethnicities are included in the factor ethnicity group. On the other hand, the random effect is the factors where its effects are random, where they are assumed to be drawn randomly from a distribution during the data-generating process. In this study, the study sample is a random sample of the target population of food handlers at food premises and the study needs to measure KAP score of the food handlers a few times.

GLMM can incorporate both fixed and random effects. Individual's response at baseline (intercept) is allowed to differ across subjects by releasing the random effect of intercept. The change in response over time is also allowed to differ across subjects by releasing the random effect of a linear slope. By adding the random effects in the model, GLMM provides estimated parameters (fixed effect) and individual variability of these parameters around the population trend (Ellison, 2017).

All results of log-transformed data considered underlying data transformation in result interpretation. The confidence interval will be set at 95% for mean estimations. The level of significance, alpha ( $\alpha$ ), will be set at 0.05. A p-value of less than 0.05 pertained to the decision rule. The dependent variables measured in this study are the outcome (primary and secondary) and effectiveness of the SCT constructs as the base of theory-based intervention module in occupational safety and health training among food handlers.

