### **1.5.2 SPECIFIC OBJECTIVE**

The specific objectives of this study are:

1. To describe the baseline sociodemographic, socioeconomic, working experience, training attendance, and means KAP score of food handlers.
2. To develop and implement a theory-based intervention module for food handlers in Selangor, Malaysia.
3. To evaluate the effectiveness of the SCT constructs as the main framework of the intervention module in improving KAP among food handlers between the intervention and control group.

4. To describe and compare the effectiveness of the TRIM-OSH on the change of knowledge, attitude and practice compared to standard training among food handlers between and within groups at the end, and one-month post training, after controlling for covariates.

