## 1.6 RESEARCH HYPOTHESIS

The research hypothesis of this study is:

- H1:** The sociodemographic, socioeconomic, working experience, and training attendance characteristics of the intervention and control groups would be the same.
- H01:** There is no significant differences in the sociodemographic, socioeconomic, working experience, and training attendance characteristics of the intervention and control groups.
- H2:** The KAP on occupational safety and health at food premises of the intervention and control groups at the baseline would be the same.
- H02:** There is no significant differences in the KAP on occupational safety and health at food premises of the intervention and control groups at the baseline.
- H3:** The SCT constructs as the main framework of the intervention module is effective in improving KAP among food handlers between the intervention and control group.
- H03:** The SCT constructs as the main framework of the intervention module have no significant effect in KAP among food handlers between the intervention and control group.
- H4:** The TRIM-OSH effectively improves KAP on occupational safety and health at food premises among food handlers.

**H04:** There is no significant differences in the KAP on occupational safety and health at food premises of the intervention and control groups at post-intervention.

## CHAPTER 2

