| Post-intervention                                                         |               |    |           |
| 1-month                                                                   |               |    |           |

\*Repeated measure ANOVA

\*\*Bonferroni adjustment

\*\*\*Significant at  $p < 0.05$

Table F. Fixed Coefficient of variables for self efficacy on occupational safety and health at food premises

| Variable          | Coefficients | Std. Error | t | p-value | 95% CI |       |
|-------------------|--------------|------------|---|---------|--------|-------|
|                   |              |            |   |         | Lower  | Upper |
| Group      |              |            |   |         |        |       |
| Intervention      |              |            |   |         |        |       |
| Control           |              |            |   |         |        |       |
| Time       |              |            |   |         |        |       |
| Baseline          |              |            |   |         |        |       |
| Post-intervention |              |            |   |         |        |       |
| 1-month           |              |            |   |         |        |       |
| Education  |              |            |   |         |        |       |
| Primary           |              |            |   |         |        |       |
| Secondary         |              |            |   |         |        |       |
| Tertiary          |              |            |   |         |        |       |

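### H3 claims that the SCT framework improves KAP between arms, but no analysis in section 3.10 or the dummy tables tests that claim

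*Combined protocol and SAP*

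**What the plan says.** Objective 3 in section 1.5.2 is "To evaluate the effectiveness of the SCT constructs as the main framework of the intervention module in improving KAP among food handlers", comparing the two groups. The matching null, H03 in section 1.6, is that the SCT constructs, as the framework of the module, "have no significant effect in KAP among food handlers between the intervention and control group". H4 and Objective 4 separately cover the effect of TRIM-OSH on KAP against standard training.

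Section 3.10 first describes a GLMM for the effects of sociodemographic, socioeconomic, experience and training factors on KAP. It then plans a further analysis of "the effects of SCT constructs component as the base of the theory-based intervention module which is behavior, individual and environment factors on KAP", which, it continues, "pre and post intervention within and between study groups will be determined". No model term, contrast or decision rule is tied to H3. The only rule is general: "A p-value of less than 0.05 pertained to the decision rule". The same section also lists "effectiveness of the SCT constructs as the base of theory-based intervention module" among the dependent variables.

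The dummy tables in section 4.1 treat the constructs as outcomes. Table B compares the self-efficacy, behavioural capacity and supportive-environment totals between groups at each of three visits by Mann-Whitney test. Tables C to E compare visits within each group by repeated-measures ANOVA. Table F, "Fixed Coefficient of variables for self efficacy on occupational safety and health at food premises", has rows for group, time and education.

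**The concern.** H03 can be false only if something differs between the arms. A coefficient of a construct on KAP has a different null: that the two scores are unrelated across people. Workers with more self-efficacy or a more supportive workplace may well report better attitude and practice before any training, and in the control arm too. Where both scores are self-reported, shared reporting style can add to the association. Randomisation plays no part in such a coefficient.

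The dummy tables fail in the other direction. A rise in self-efficacy with no change in KAP would look like support for the constructs, although H3 is about KAP.

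At stake is the mechanism claim. H3 could be reported as supported by an association that was there at baseline. If H4 succeeded, that association could be presented as evidence that the SCT framework was the reason. If H4 failed, H3 could still be declared supported.

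**Working it through.** **Step 1. The plan's routes to H3 side by side.**

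| Place | Outcome | Predictor or comparison | Links arm, construct and KAP? |
|---|---|---|---|
| 1.6, H03 | KAP | SCT framework, between arms | this is the claim |
| 3.10, SCT analysis | KAP | behaviour, individual and environment factors | no arm contrast written |
| 3.10, dependent variables | effectiveness of SCT constructs | not stated | no |
| Table B | three construct totals | arm, at each visit | no KAP |
| Tables C to E | construct totals | visit, within each arm | no KAP; not between arms |
| Table F | self-efficacy | group, time, education | no KAP; no group-by-time row |

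The wording about comparisons within and between groups does not supply the missing contrast. The preceding GLMM sentence attaches the same wording to age, gender, ethnicity and education, which are plainly predictors of KAP.

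**Step 2. Sample sizes.** Section 3.6 starts from 20 clusters of 6 and allows 20% attrition at each of three follow-ups: 6 / 0.8³ = 11.72, rounded up to 12, and 20 × 12 = 240. This reproduces the stated N. The executive summary gives 139. Both are used below. The plan states no error rate or power for H3, so there is no figure of its own to reproduce on that point.

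**Step 3. Rejection with an inert module, one measurement per person.** Suppose the construct coefficient decides H3. With no module effect, its rejection rate is the power to detect the background correlation r. By Fisher's z, with a two-sided 0.05 test (the plan does not state sidedness) and independent people:

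x = atanh(r) × √(N − 3); rejection = Φ(x − 1.96) + Φ(−x − 1.96).

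For r = 0.1 and N = 139: x = 0.1003 × √136 = 1.170; Φ(−0.790) + Φ(−3.130) = 0.215 + 0.001 = 0.216.

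For r = 0.2 and N = 240: x = 0.2027 × √237 = 3.121; Φ(1.161) = 0.877.

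| r (assumed) | N = 139 | N = 240 |
|---|---|---|
| 0 | 5% | 5% |
| 0.05 | 9% | 12% |
| 0.1 | 22% | 34% |
| 0.2 | 66% | 88% |
| 0.3 | 95% | 99.7% |

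Rejection passes 50% at r of about 0.17 (N = 139) or 0.13 (N = 240).

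**Step 4. Three visits analysed jointly.** This is a simulation with no module effect on constructs or KAP: 20 clusters, 1,500 runs per cell, assumed within-person correlation 0.6, cluster ICC 0.05, and the same r between and within people. The construct coefficient, adjusted for group, time and their interaction, rejects as follows.

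| r (assumed) | N = 140 | N = 240 |
|---|---|---|
| 0 | 5% | 5% |
| 0.05 | 18% | 27% |
| 0.1 | 52% | 77% |
| 0.2 | 98% | 100% |

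In the same simulated trials a group-by-post test, on KAP or on a construct score, rejects in about 4% to 7% at every r. The excess therefore comes from which coefficient is tested.

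**The case against.** The strongest reply is that the plan never commits to the construct coefficient. The sentence in 3.10 mentions comparisons between groups and could mean the module's SCT components and not participants' scores. SCT effectiveness is also called a dependent variable, and Table B already compares all three constructs between arms. A between-arm comparison of construct scores is not inflated by the construct-KAP correlation.

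Much of this stands. It shows that the plan is ambiguous and that part of a sound analysis is already there. It does not produce a test of H03, because the tables that use the arm contrast leave KAP out, and the sentence that includes KAP writes no arm contrast.

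A reader might go further and infer that H03 would normally be rejected with an inert module. The documents do not support that. It needs one reading of an unclear sentence and a correlation they do not give. At r = 0.05 with one measurement per person the rate is only 9% to 12%.

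A reader might also infer that the trial's main effectiveness conclusion is at risk. It is not: KAP scores are the listed outcomes in the variables section, and H4 compares them between arms.

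Finally, the choice of mediation method is partly a matter of convention, and an interval that resamples whole clusters is fragile with 20 clusters in total. That limits how firmly any one method can be prescribed.

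**Conclusion.** The concern holds as a specification gap with a possible invalid conclusion attached. H3 has no defined estimand, model term or decision rule. Section 3.10 and the dummy tables put the constructs on opposite sides, and no route links arm, construct and KAP.

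If p<0.05 on the construct coefficient were taken as the answer to H3, the false-support rate would be well above 5% once the scores are modestly correlated. The size depends on an assumed correlation, a two-sided test and, for the one-measurement figures, independent people. With three visits modelled jointly the rates are higher, under the further assumptions listed above. The conclusion is confined to H3 and Objective 3. The gap should be closed before the data are analysed.

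**What to change.** In section 3.10:

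1. State that construct-on-KAP coefficients are descriptive associations and do not decide H3. Keep construct scores out of the model that tests H4, since they are measured after allocation and may carry part of the module's effect.
2. Test the between-arm difference in each construct after training, adjusted for its baseline value and for clustering, in place of the unadjusted Mann-Whitney tests in Table B. Add the matching contrast to Table F.
3. Claim that a construct explains a KAP gain only on a pre-specified indirect effect from arm through construct to KAP, adjusted for baseline construct and baseline KAP. Its interval should respect the clusters, and the assumption of no unmeasured confounding between construct and KAP should be stated. This path matches the module outline, whose three sessions target self-efficacy, supportive environment and behavioural capability in turn. If this analysis is not wanted, restrict H3 and Objective 3 to the construct outcomes.
4. Confirm that construct scores are collected at all three visits. Section 3.7 lists four questionnaire parts, none for SCT constructs, and section 3.9 names only the KAP score at one month. The questionnaire itself is not in the supplied text.

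The cost is wording and one added analysis, with no extra participants or visits. If construct scores are not yet collected, questionnaire items are needed as well. H3 becomes harder to support, and with few clusters the indirect-effect interval may be wide.

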### **3.2 Study design**

The study is a randomized controlled trial study. A single blinded, cluster randomized controlled trial study design will be conducted with pre-assessment and post-assessment on the intervention module. The respondents will be divided into two groups, intervention or control. The control group will receive a standard treatment and brochures related to occupational safety and health, while the intervention group will receive a theory-based intervention module on occupational safety and health among food handlers. The duration of the study is within 3-6 months.

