### 3.5 Sampling technique

There are 324 Food Handler Training Schools in Selangor located in nine districts. This study will use a simple random sampling technique to select the sampling location. Four districts will be randomly selected. Once the district is determined, the selection of the Food Handler Training School within the district will proceed by using a similar method and subsequently assigned. The flow of the sampling technique is shown in the figure below:

[figure not shown]

Figure 5. Cluster random sampling flow chart.

Cluster randomization will be used to ensure administrative efficacy, lessened risk of experimental contamination, and enhancement of subject compliance. The participants attending the food handler training program will be invited into the study via invitation and assessed for eligibility. The unit of randomization will be on a 1:1 basis in either the control or intervention group.

An independent research staff, blinded as to whether they were nominating within the control or an intervention group and unaware which of their participants had consented to participate.

[figure not shown]

Figure 6. Proposed research Flow Chart

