| The total score of self efficacies                |                    |                   |         |
| Control                                                  |                    |                   |         |
| Intervention                                             |                    |                   |         |
| Man-Whitney U Test                                       |                    |                   |         |
| p-value                                           |                    |                   |         |
| The total score of behavioral capacity            |                    |                   |         |
| Control                                                  |                    |                   |         |
| Intervention                                             |                    |                   |         |
| Man-Whitney U Test                                       |                    |                   |         |
| p-value                                           |                    |                   |         |
| The total score of supportive working environment |                    |                   |         |
| Control                                                  |                    |                   |         |
| Intervention                                             |                    |                   |         |
| Man-Whitney U Test                                       |                    |                   |         |
| p-value                                           |                    |                   |         |

Significant at  $p < 0.05$

Table C. Within intervention group difference of total score of self-efficacies on occupational safety and health at food premises.

| Self-efficacy on occupational safety and health at food premises | Mean $\pm$ SD | F* | p-value** |
|------------------------------------------------------------------|---------------|----|-----------|
| Within Intervention group.                                       |               |    |           |
| Baseline                                                         |               |    |           |
| Post-intervention                                                |               |    |           |
| 1-month                                                          |               |    |           |

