| Within Control Group                                             |               |    |           |
| Baseline                                                         |               |    |           |
| Post-intervention                                                |               |    |           |
| 1-month                                                          |               |    |           |

\*Repeated measure ANOVA

\*\*Bonferroni adjustment

\*\*\*Significant at  $p < 0.05$

Table D. Within intervention group difference of total score of behavioral capacity on occupational safety and health at food premises.

| Behavioral capacity on occupational safety and health at food premises | Mean $\pm$ SD | F* | p-value** |
|------------------------------------------------------------------------|---------------|----|-----------|
| Within Intervention group.                                             |               |    |           |
| Baseline                                                               |               |    |           |

|                      |  |  |  |
|----------------------|--|--|--|
| Post-intervention    |  |  |  |
| 1-month              |  |  |  |
| Within Control Group |  |  |  |
| Baseline             |  |  |  |
| Post-intervention    |  |  |  |
| 1-month              |  |  |  |

\*Repeated measure ANOVA

\*\*Bonferroni adjustment

\*\*\*Significant at  $p < 0.05$

Table E. Within intervention group difference of total score of supportive working environment on occupational safety and health at food premises.

| Supportive environment on occupational safety and health at food premises | Mean $\pm$ SD | F* | p-value** |
|---------------------------------------------------------------------------|---------------|----|-----------|
| Within Intervention group.                                                |               |    |           |
| Baseline                                                                  |               |    |           |
| Post-intervention                                                         |               |    |           |
| 1-month                                                                   |               |    |           |
| Within Control Group                                                      |               |    |           |
| Baseline                                                                  |               |    |           |

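### The trial randomises clusters, but neither the GLMM nor the Table B tests account for the cluster, so between-arm results are too favourable if scores correlate within clusters

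*Combined protocol and SAP*

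**What the plan says.** The design is clustered. Section 3.2 (Study design) states: "A single blinded, cluster randomized controlled trial study design will be conducted with pre-assessment and post-assessment on the intervention module". Section 3.5 gives the reasons: "Cluster randomization will be used to ensure administrative efficacy, lessened risk of experimental contamination, and enhancement of subject compliance". It also describes the sampling: "Four districts will be randomly selected", then training schools within them, with 1:1 allocation. Section 3.6 (Sample size) counts in clusters and arrives at 20 clusters of 12, N = 240.

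The analysis is not clustered. Section 3.10 says that an individual's "response at baseline (intercept) is allowed to differ across subjects by releasing the random effect of intercept", and then: "The change in response over time is also allowed to differ across subjects by releasing the random effect of a linear slope". It justifies these terms by food handlers being sampled at random and measured several times.

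In section 4.1, Table B compares the arms at baseline, post-intervention and one month with a "Man-Whitney U Test". Tables C to E use "Repeated measure ANOVA" within each arm. Table F, the GLMM layout for self-efficacy, has rows for group, time and education, with no cluster term and no group-by-time row.

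The readable text mentions no school or district effect, ICC, design effect, robust standard error or cluster-level analysis.

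**The concern.** Everyone in a cluster is in the same arm, so the difference between arms has to be judged against the variation between clusters. A subject intercept and slope absorb the correlation among one person's repeated scores. They do not absorb correlation between different people in the same cluster. Participants are recruited and assessed through selected training schools (sections 3.5 and 3.9), so some correlation of that kind is plausible.

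Section 3.10 makes p < 0.05 the decision rule. If the standard error of the arm contrast is understated, the module can be declared effective more often than 5% of the time when it has no effect, and the reported intervals will be too narrow.

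**Working it through.** **The plan's own figure.** Section 3.6 starts from 6 per cluster and allows 20% loss at each of three follow-ups: 6 / 0.8³ = 11.72, rounded up to 12; 20 × 12 = 240. This reproduces the stated N. I read the 20 clusters as the trial total, because that is what gives 240. The starting figure of 20 clusters of 6 cannot be rebuilt, since no effect size, SD, power or ICC is given.

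**Inputs for the check.**
- Cluster size m: 12 as enrolled and about 6 after attrition (section 3.6); 139/20 = 6.95 if the Executive Summary total of 139 is spread over 20 clusters; 240/4 = 60 if the four districts in section 3.5 are the units.
- Alpha 0.05 (section 3.10), taken as two-sided because the plan does not say.
- ICC: assumed 0.01, 0.05 and 0.10.

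**Formulas.** Design effect DE = 1 + (m − 1) × ICC. The naive standard error is too small by a factor √DE. Actual type I error = 2 × (1 − Φ(1.96/√DE)).

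Example with m = 12 and ICC 0.05: DE = 1 + 11 × 0.05 = 1.55; √1.55 = 1.245; 1.96/1.245 = 1.574; two-sided tail 11.5%.

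| People per cluster | ICC 0.01 | ICC 0.05 | ICC 0.10 |
|---|---|---|---|
| 12 (20 clusters) | DE 1.11, 6.3% | DE 1.55, 11.5% | DE 2.10, 17.6% |
| 6 retained (20 clusters) | DE 1.05, 5.6% | DE 1.25, 8.0% | DE 1.50, 11.0% |
| 6.95 (139 in 20 clusters) | DE 1.06, 5.7% | DE 1.30, 8.5% | DE 1.60, 12.1% |
| 60 (4 districts) | DE 1.59, 12.0% | DE 3.95, 32.4% | DE 6.90, 45.6% |

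At ICC 0.05, nominal 95% intervals cover 88.5% with 12 per cluster and 92.0% with 6.

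**Simulation with no true effect, 20 clusters of 12.** At ICC 0.01 / 0.05 / 0.10:
- A person-level t-test rejected in 6.1% / 11.3% / 18.3% of 10,000 runs.
- A Mann-Whitney test rejected in 6.5% / 10.7% / 17.1% of 2,000 runs.
- A t-test on cluster means (20 − 2 = 18 df) rejected in 4.8% / 4.9% / 5.1% of 10,000 runs.

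**Level or change.** This simulation used three visits with subject intercept, slope and residual variances of 0.5, 0.1 and 0.4 (assumed), and tested each contrast without a cluster term.

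| Clusters differ in | Group main effect | Group-by-time |
|---|---|---|
| Level only, ICC 0.05 | 13.2% | 4.9% |
| Level and change, ICC 0.05 | 15.6% | 11.3% |
| Level and change, ICC 0.10 | 23.2% | 17.6% |

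A group-by-time contrast is therefore inflated only when clusters differ in change. A group main effect is inflated by level differences alone, as is a comparison at one visit.

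**The case against.** A reader might infer several stronger claims that the documents do not support.

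- **That the primary results are bound to be too favourable.** Section 3.6 (Variables) defines the primary outcomes as changes in mean score. If clusters differ only in level, a group-by-time test holds its size (4.9% above). The inflation there is conditional. This objection limits the point but does not remove it: Table F has no group-by-time row, and nothing rules out clusters differing in change.
- **That schools are the randomised unit.** Section 3.5 selects districts and then schools without saying which is allocated, and section 3.3.1 calls the individual the sampling unit. Figures 5 and 6 are not shown and may settle it. The omission matters under either reading.
- **That people in a cluster share a trainer, class or employer.** No passage says so. The first delivery mode listed for each module session is a web-based course, and Table A allows for self-employed, student and unemployed participants. This bears on how large the ICC is, not on whether to model it.
- **That every planned test feeds the efficacy claim.** The repeated-measures ANOVA is within arm. The chi-square is planned for associations between categorical variables, which fits the baseline comparison in Table A. Tables B to F concern the theory constructs, not knowledge and attitude. The claim about the primary outcomes rests on the GLMM.
- **That the figures for 12 per cluster, or for four districts, are the expected size.** With about 6 retained the inflation is smaller, and the district figures apply only if districts were allocated.

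SPSS mixed models can hold a cluster effect and an analyst might add one, but the plan does not ask for it.

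**Conclusion.** The point stands in conditional form. The design and sample size sections are clustered, and the analysis specification has no term for the randomised cluster. Following section 3.10 and Table B as written understates the error of between-arm comparisons whenever the compared quantity varies between clusters: level for single-visit comparisons and group main effects, change for group-by-time.

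The direction is certain for any positive ICC. The size is not, because the documents give no ICC. Over the assumed range of 0.01 to 0.10, actual type I error is about 5.6% to 11.0% with 6 retained per cluster and 6.3% to 17.6% with 12. If the four districts are the units, at 60 people each, it is 12.0% at ICC 0.01 and 32.4% at 0.05. These figures assume equal cluster sizes and, outside the district case, 20 clusters in total.

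It should be corrected before analysis, because it affects the main between-arm inference and readers cannot correct for it unless cluster is recorded.

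**What to change.** In section 3.10:

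1. Name the randomised unit (school or district) and record its ID for every participant.
2. Add a random intercept for that unit, and a unit-by-time term where it can be estimated, with subjects nested in the unit. Use small-sample degrees of freedom, for example Satterthwaite.
3. Check the result with a t-test on cluster-mean changes, on the number of clusters minus 2 degrees of freedom.
4. Replace the Mann-Whitney p-values in Table B with results from the same clustered model.
5. Fit district as a fixed effect only if schools are the allocated unit and both arms occur within districts. If districts are allocated, a fixed district effect is aliased with arm.

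The direct cost is analysis-plan wording and one ID column; allocation, visits and recruitment do not change. The real cost is precision. With 12 per cluster, intervals widen by √1.55 − 1 = 24% at ICC 0.05 and √2.10 − 1 = 45% at ICC 0.10. A difference that 240 independent people would detect with 80% power has about 57% power at ICC 0.05 with 20 clusters (18 df). If the four districts are the units, only 4 − 2 = 2 df remain and the same difference has about 14% power. The sponsor should therefore settle the unit first.
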